## Introduction

Stroke represents a significant global public health issue, and increasing incidence rates have substantially contributed to the national disease burden in Bangladesh [1]. The Global Burden of Disease Study 2019 identified stroke as a leading cause of death and disability-adjusted life years in South Asian populations, with Bangladesh experiencing particularly high stroke mortality rates, which may be attributed to an underdeveloped primary healthcare system and persistent financial constraints [2]. Current risk prediction models, predominantly developed in Western populations, inadequately capture the complex interplay of socioeconomic, environmental, and mental health factors prevalent in Bangladesh [3]. Recent advances in artificial intelligence (AI) have revolutionized stroke prediction capabilities, with ensemble learning methods achieving accuracies up to 99% and incorporating explainable AI techniques for enhanced clinical interpretability [4,5,6]. However, these sophisticated models remain largely untested in Bangladeshi populations, where unique risk factors, including high rural population density, limited healthcare access, and significant socioeconomic disparities, influence stroke outcomes [6]. Traditional risk assessment tools fail to account for these contextual factors, resulting in suboptimal predictions and missed opportunities for prevention [7].

Emerging evidence suggests that mental health comorbidities, particularly anxiety and depression, significantly influence stroke risk through complex pathophysiological mechanisms, including chronic inflammation, endothelial dysfunction, and behavioral factors [8,9]. Despite this growing recognition, the relationship between mental health and stroke remains underexplored in Bangladeshi populations, where cultural stigma and limited mental health resources create additional barriers to comprehensive care [10]. Furthermore, educational attainment and rural-urban residence patterns in Bangladesh create distinct risk profiles that require specialized modeling approaches to achieve optimal prediction accuracy [11].

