## Materials and methods

The FORECAST study is an ongoing ambispective case-control study conducted at the National Institute of Neurosciences and Hospital (NINS&H), Bangladesh, in collaboration with the Institute of Cardiovascular Research, Royal Holloway, University of London, UK. This design allows for comprehensive characterization of stroke risk factors while maintaining feasibility within the Bangladeshi healthcare infrastructure between May 2022 and April 2026. The primary objective is to develop an AI-based risk prediction model that identifies independent predictors of stroke occurrence and poor long-term outcomes among Bangladeshi individuals. The study will also utilize explainable AI techniques to enhance the clinical interpretability of CT and MRI brain imaging findings, leveraging recent advances in stroke prediction modeling, with an anticipated accuracy rate exceeding 90%.

The study has received ethics approval from the institutional review boards of the National Institute of Neurosciences and Hospital (NINS&H), Dhaka, Bangladesh (reference number IRB/NINS/2025/492). Given the retrospective nature of case identification, a waiver of informed consent has been granted for historical data analysis, while prospective participants will provide written informed consent. Data anonymization follows international standards with secure storage and restricted access protocols. Written informed consent will also be obtained from a legal representative if the patient is unconscious or intubated.

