Feature selection will employ correlation-based, mutual information-based, and wrapper-based methods to identify optimal predictor combinations while minimizing overfitting [20]. The study will address data imbalance issues through the Synthetic Minority Oversampling Technique (SMOTE) and other resampling methods to ensure robust model performance across all risk categories [21]. Model validation will utilize k-fold cross-validation (k = 10) with stratified sampling to ensure representative distribution across subgroups [22]. Performance evaluation will encompass accuracy, sensitivity, specificity, area under the receiver operating characteristic curve (AUC-ROC), and F1-score metrics, with target performance exceeding 90% accuracy based on recent advances in stroke prediction modeling [23,24].

To enhance clinical interpretability and trust, the study will integrate explainable AI techniques, including Shapley Additive Explanations (SHAP) and Local Interpretable Model-Agnostic Explanations (LIME) [25]. These methods will provide insights into feature importance, individual prediction explanations, and model decision-making processes, facilitating clinical adoption and regulatory approval (Figure 1).

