**Figure 1 FIG1:**
[figure not shown]
Dummy flowchart showing case-control recruitment to dissemination GAD: generalized anxiety disorder; PHQ: Patient Health Questionnaire; AI: artificial intelligence; AUROC: area under the receiver operating characteristic curve; mRS: Modified Rankin Scale Image created by the authors

Statistical analysis

Statistical analyses will employ appropriate methods for case-control studies, including conditional logistic regression for matched data and multiple imputation for missing values. Subgroup analyses will examine risk patterns across rural-urban populations, educational strata, and age groups to identify population-specific risk factors. Model calibration will be assessed using Hosmer-Lemeshow goodness-of-fit tests and calibration plots [26].

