## Results

Expected results and clinical impact

The FORECAST study will deliver the first AI-based stroke prediction model (Figure 2) specifically designed for Bangladeshi populations, with expected clinical and scientific impacts encompassing improved risk stratification leading to targeted prevention strategies, novel insights into mental health-stroke associations in South Asian populations, and cost-effective screening tools for resource-limited settings [27]. The model will provide personalized risk scores with confidence intervals, enabling clinicians to make evidence-based decisions regarding preventive interventions and resource allocation.

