## Discussion

The development of AI-based risk prediction models for stroke represents a paradigm shift in preventive neurology, offering unprecedented opportunities to enhance primary prevention strategies and improve patient outcomes [4,5]. Traditional stroke risk assessment tools, while valuable, demonstrate significant limitations in capturing the multifaceted nature of stroke pathogenesis, particularly in diverse populations with unique socioeconomic and cultural contexts [29]. The integration of AI technologies addresses these limitations by processing vast amounts of complex, interconnected data to identify subtle patterns and risk associations that conventional statistical methods may overlook.

The importance of developing population-specific prediction models cannot be overstated, particularly for Bangladesh, where conventional Western-derived risk calculators demonstrate poor calibration and discrimination [30]. The FORECAST study's focus on incorporating mental health variables represents an important advance, given emerging evidence linking depression and anxiety to increased stroke risk through mechanisms including chronic systemic inflammation, endothelial dysfunction, and poor medication adherence [29,30]. Furthermore, the inclusion of socioeconomic determinants such as rural-urban residence and educational attainment addresses critical social determinants of health that significantly influence stroke outcomes in resource-limited settings.

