The clinical implications of accurate AI-based risk prediction extend beyond individual patient care to encompass population health strategies and healthcare resource allocation. By identifying high-risk individuals before stroke event occurrence, clinicians can implement targeted interventions, including intensive blood pressure management, anticoagulation therapy, lifestyle modifications, and mental health support, potentially preventing thousands of strokes annually [12,30]. Moreover, the explainable AI components of the FORECAST model will enhance clinical adoption by providing transparent, interpretable risk assessments that support shared decision-making between patients and healthcare providers, ultimately improving treatment adherence and outcomes. While the proposed study is promising, there are several limitations to consider. The sample size may not fully reflect the clinical and environmental diversity of the Bangladeshi population, which could affect how well the AI-based stroke risk prediction model applies to broader groups. The AI-based risk prediction model offers a powerful tool for identifying potential risk factors and predicting long-term poor prognosis among stroke patients in Bangladesh. Its strength lies in the ability to analyse large, complex datasets, uncovering subtle patterns that may not be apparent through traditional statistical methods. By integrating demographic, clinical, and imaging data, the model can provide personalised risk assessments to support early intervention and improve patient outcomes. However, limitations include dependence on data quality and completeness, as inconsistencies or biases in local healthcare records may reduce accuracy. In addition, the model’s generalisability may be constrained by limited external validation, making it essential to test and refine it across diverse populations and clinical settings within Bangladesh. Data will mostly come from selected hospitals, so rural or underserved populations may not be represented, especially where healthcare access and reporting differ. Further, the AI model’s accuracy depends on data quality, which could be affected by inconsistent diagnostic criteria, missing data, differences in imaging protocols, or variations in lab measurements. Moreover, without external validation using independent, multi-center groups, the model’s usefulness outside the study population is limited. The AI algorithm’s complex nature may also make it harder to interpret results for clinical decisions.

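### The article claims improvement over traditional tools and methods, but fixes only an absolute accuracy target above 90% for the new model alone, which cannot show whether machine learning or the new variables add anything

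*Protocol article*

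**What the plan says.** The objective in Materials and methods is developmental and names no comparator: "The primary objective is to develop an AI-based risk prediction model that identifies independent predictors of stroke occurrence and poor long-term outcomes".

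The comparative statements stand elsewhere in the article:
- Introduction: "Traditional risk assessment tools fail to account for these contextual factors, resulting in suboptimal predictions and missed opportunities for prevention".
- Results, expected impact: "improved risk stratification leading to targeted prevention strategies".
- Discussion, on existing scores in Bangladesh: "conventional Western-derived risk calculators demonstrate poor calibration and discrimination".
- Discussion, on the new variables: the study's "focus on incorporating mental health variables represents an important advance".
- Discussion, on the method: "uncovering subtle patterns that may not be apparent through traditional statistical methods".

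The evaluation is in the performance paragraph of Materials and methods. It lists accuracy, sensitivity, specificity, AUC and F1 under stratified 10-fold cross-validation, "with target performance exceeding 90% accuracy based on recent advances in stroke prediction modeling". The Statistical analysis section adds a Hosmer-Lemeshow test and calibration plots, and names "conditional logistic regression for matched data and multiple imputation for missing values" as methods for the case-control data.

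**The concern.** A claim of improvement needs an estimate of a difference: the new model against an existing one, or the model with the new variables against the model without them. Every measure described concerns the ensemble by itself. The one figure that performance is held to comes from other studies' data. Accuracy depends on case mix and on how controls are chosen. Here the controls are healthy, matched on age and sex, drawn from similar geographic and socioeconomic backgrounds, and taken 1:1, so a figure from another dataset cannot stand in for a comparator.

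If the plan is followed as written, passing 90% leaves open that a plain regression on hypertension, diabetes and smoking does as well in the same people. Missing 90% leaves open that the new variables help appreciably. Either way, the statements about improved stratification and about patterns beyond traditional methods would be published with no estimate behind them.

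**Working it through.** **1. Claim against evaluation.**

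| Claim in the article | What would estimate it | What is described |
|---|---|---|
| Better than existing or Western tools | An existing score applied to the same participants | Not described |
| Mental-health and social variables are an advance | Model with minus model without them, same folds | Not described; SHAP and LIME show how a fitted model uses its features, not added predictive value |
| AI finds what traditional methods miss | Ensemble minus regression on the same inputs | Conditional logistic regression is named for the matched data, not as a benchmark |
| Accuracy above 90% | Accuracy of one model | Described, with a target |

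**2. The 90% target is precise but uninformative about a difference.** With 4,000 participants, the 95% half-width at 90% accuracy is 1.96 × √(0.9 × 0.1 / 4,000) = 0.0093, about 0.9 points. The study can judge the target well, but the answer says nothing about another model.

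**3. Would the target register a real gain?** Inputs from the sample-size paragraph: 35%, 15% and a minimum detectable odds ratio of 2.0. The two percentages imply (0.35/0.65)/(0.15/0.85) = 3.05, not 2.0, so both values are carried.

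Assumptions (not in the plan): independent binary factors of equal strength, an unweighted count as the predictor, and 35% and 15% read as exposure prevalence in cases and controls. The article labels them stroke prevalence by exposure; the odds ratio is the same under either reading. For an odds ratio of 2.0 from 15%, odds = 2 × 0.15/0.85 = 0.353, so prevalence in cases is 0.353/1.353 = 0.261.

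With k factors the count is Binomial(k, p₁) in cases and Binomial(k, 0.15) in controls. Best-cut accuracy at 1:1 = ½ Σ max(f₁, f₀). AUC = P(case count > control count) + ½ P(tie).

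| k | OR 3.05: accuracy / AUC | OR 2.0: accuracy / AUC |
|---|---|---|
| 8 (conventional only) | 74.4% / 0.821 | 65.8% / 0.704 |
| 10 (two added) | 77.9% / 0.849 | 66.3% / 0.727 |
| 12 (four added) | 79.2% / 0.872 | 68.9% / 0.747 |

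Accuracy gain over k = 8:
- OR 3.05: 3.5 points (two added), 4.8 points (four added).
- OR 2.0: 0.5 points (two added), 3.1 points (four added).

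All six cells miss 90%, so in this illustration the target gives the same answer whether or not the added factors help. Accuracy is also a coarse measure of the gain: at OR 2.0, two added factors raise AUC by 0.023 but accuracy by only 0.5 points.

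**4. Could the planned enrolment carry a paired comparison?** The Hanley-McNeil standard error of one AUC, with 2,000 per group or 1,700 (2,000 × 0.85, the plan's 15% allowance), is:
- AUC 0.80: 0.0070 (2,000) and 0.0076 (1,700).
- AUC 0.90: 0.0050 (2,000) and 0.0055 (1,700).

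The half-width for a paired difference is 1.96 × SE × √(2(1 − r)), with assumed correlation r between the two AUCs:
- Widest: AUC 0.80, 1,700 per group, r = 0.5: 1.96 × 0.0076 × 1 = 0.0149.
- Narrowest: AUC 0.90, 2,000 per group, r = 0.9: 1.96 × 0.0050 × 0.447 = 0.0044.

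These values ignore the matching and the overlap of training folds, so they indicate order of size only. They take the stated enrolment as given and do not rest on the sample-size calculation, which concerns a single exposure association.

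**The case against.** **The objective is not comparative.** This is correct. Developing a model without a head-to-head test is legitimate, and the comparative statements are in the Introduction, the expected impact and the Discussion. A reader might infer that the study's formal question is relative and that the design fails to answer it. The stated objective does not support that. The point is a mismatch between the article's claims and its evaluation.

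**The 90% is neither the only yardstick nor a declared success criterion.** Also correct. Five metrics and calibration are planned, and the figure appears variously as an expectation, an anticipation and a target, with no decision attached. It is the only numerical target, and the remaining measures also concern the new model alone.

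**Benchmarks may be in the full protocol or analysis plan.** They may, and their absence from a condensed article is not itself a fault. Wrapper-based feature selection also scores predictor subsets by performance, so comparison of predictor sets is not wholly absent. But it is a selection step and yields no reported contrast for the mental-health or social modules. What stands is that the article fixes a target that does not answer the claim it makes.

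**The size of the gain is not the plan's.** This stands. The gain depends on the odds ratio, on relabelling the 35% and 15%, and on equal, independent factors. The article also collects continuous measurements, so the calculation does not show that 90% is unattainable. It shows only that a modest gain can leave the target's answer unchanged.

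**A contrast in this sample has its own biases.** This stands too. Socioeconomic matching suppresses social predictors. The timing of GAD-7 and PHQ-9 relative to the stroke is not stated.

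**Conclusion.** The concern holds as a mismatch. The article describes development but argues improvement, while its only numerical target is an absolute accuracy borrowed from other studies and all its other checks describe one model. Following it as written gives no estimate of what machine learning or the new variables contribute, whichever side of 90% the result falls.

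The size of what goes unmeasured is illustrative only: about 3.5 to 5 accuracy points at an odds ratio of 3.05 and about 0.5 to 3 at 2.0, under independent, equally strong binary factors. Under the stated assumptions, enrolment is ample to estimate an AUC difference to within about 0.004 to 0.015. What the evaluation lacks is a comparator, not participants.

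**What to change.** In the performance paragraph of Materials and methods, replace the accuracy target with a prespecified paired comparison in the same 10 folds:

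- (a) penalised logistic regression on the conventional clinical and lifestyle variables;
- (b) the same regression with GAD-7 and PHQ-9 added, and the sociodemographic variables entered as a separate step, so that each set has its own contrast;
- (c) the ensemble on the same inputs as the full regression.

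Report differences in AUC and in calibration with 95% confidence intervals, using a method that respects both the matching and the cross-validation. The steps within (b), each against the model before it, give the value of the new variables. The ensemble minus the full regression gives the value of machine learning.

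State with the results that:
- the comparison applies within this matched sample;
- matching on age, sex, geographic and socioeconomic background pushes any social-factor gain toward null;
- a GAD-7 or PHQ-9 gain may reflect the stroke itself if the scales are scored after onset.

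Make no claim of superiority over Western risk scores unless one that can be computed from the collected variables is scored on the same participants; regressions (a) and (b) do not test that. If the comparison is not adopted, limit the expected-impact text to describing the performance of one developed model.

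The cost is a few regression models on data already planned and some lines of wording, with no new participants or measurements. The downside is that the headline becomes a difference that may be small or null.

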**Figure 1 FIG1:**
[figure not shown]
Dummy flowchart showing case-control recruitment to dissemination GAD: generalized anxiety disorder; PHQ: Patient Health Questionnaire; AI: artificial intelligence; AUROC: area under the receiver operating characteristic curve; mRS: Modified Rankin Scale Image created by the authors

Statistical analysis

Statistical analyses will employ appropriate methods for case-control studies, including conditional logistic regression for matched data and multiple imputation for missing values. Subgroup analyses will examine risk patterns across rural-urban populations, educational strata, and age groups to identify population-specific risk factors. Model calibration will be assessed using Hosmer-Lemeshow goodness-of-fit tests and calibration plots [26].

## Results

Expected results and clinical impact

The FORECAST study will deliver the first AI-based stroke prediction model (Figure 2) specifically designed for Bangladeshi populations, with expected clinical and scientific impacts encompassing improved risk stratification leading to targeted prevention strategies, novel insights into mental health-stroke associations in South Asian populations, and cost-effective screening tools for resource-limited settings [27]. The model will provide personalized risk scores with confidence intervals, enabling clinicians to make evidence-based decisions regarding preventive interventions and resource allocation.

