Inclusion criteria encompass complete medical records availability and Bangladeshi residency for ≥5 years, while exclusion criteria include incomplete clinical data and previous stroke history for first-ever stroke analyses. Cases include adult patients (≥18 years) with acute ischemic or hemorrhagic stroke confirmed by a neuroimaging scan, either a CT/MRI scan, evaluated by two experts (neurologist and intervention radiologist). Stroke diagnosis will follow American Stroke Association (ASA) guidelines, confirmed by clinical evaluation and CT or MRI imaging. All patients with any form or severity of stroke, including mild, severe, prior, recurrent, critically ill, or intubated cases, will be included to reduce selection and reporting bias. Individuals with major comorbidities, such as other neurological disorders (e.g., brain tumors), severe systemic illnesses (e.g., cancer), secondary strokes due to other conditions (e.g., endocarditis, trauma), or those taking medications affecting stroke risk, will be excluded. Controls comprise age and sex-matched healthy adults without stroke history, recruited from hospital visitors and community health facilities, ensuring representative sampling across urban and rural populations. Controls will be 18 years or older, have no history of stroke, and must provide written informed consent. Hospitalized individuals are not eligible as controls. If spouse controls are unavailable, age- and sex-matched community volunteers will be recruited, with gender balance ensured through equal representation or sex stratification in analysis. The study will maintain equal proportions of males and females in both groups to address sex-related differences in stroke risk. Controls will be selected from the same geographic and socioeconomic backgrounds as cases to minimize population stratification and ensure comparability in environmental factors, lifestyle, and medication use.

The study will enroll 4,000 participants, comprising 2,000 stroke cases and 2,000 matched controls. Sample size calculations utilized established formulas for case-control studies with binary exposure, assuming 80% power, 5% significance level, and expected stroke prevalence of 35% in the exposed group versus 15% in the unexposed group [12,13]. This sample size ensures adequate power to detect clinically meaningful associations while accounting for potential data missingness and subgroup analyses. The formula for case-control studies with binary exposure:

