n = [P₁(1-P₁) + P₀(1-P₀)] × (Zβ + Zα/2)² / (P₁ - P₀)²

where power (1-β): 80% (Zβ = 0.84); α: 5% (Zα/2 = 1.96), expected stroke prevalence in exposed group (P₁): 35%, expected stroke prevalence in unexposed group (P₀): 15%, and minimum detectable odds ratio: 2.0.

Calculation:

n = [0.35×0.65 + 0.15×0.85] × (0.84 + 1.96)² / (0.35 - 0.15)²

n = [0.2275 + 0.1275] × 7.84 / 0.04

n = 0.355 × 196 = 69.58 ≈ 1,740 per group

Accounting for 15% loss to follow-up and missing data: 1,740 × 1.15 = 2,000 per group

The total sample size will comprise 4,000 participants, divided into 2,000 cases and 2,000 controls.

Comprehensive data collection encompasses sociodemographic variables (age, sex, education level, rural-urban residence, occupation, income), clinical parameters (blood pressure, glucose levels, lipid profiles, body mass index), comorbidities (hypertension, diabetes mellitus, atrial fibrillation, coronary artery disease), lifestyle factors (smoking, alcohol consumption, physical activity), and mental health assessments using validated instruments including the Generalized Anxiety Disorder-7 (GAD-7) and Patient Health Questionnaire-9 (PHQ-9) scales [14,15]. Outcome measures include stroke occurrence (primary outcome) and long-term functional outcomes assessed using the Modified Rankin Scale at 90 days post-stroke (secondary outcome) [16]. Additional outcomes encompass stroke recurrence, mortality, and healthcare utilization patterns to provide comprehensive prognostic information.

The study will implement an ensemble machine learning approach integrating multiple algorithms to optimize prediction accuracy [17]. The modeling framework comprises four specialized modules: a sociodemographic module utilizing neural networks for processing education, rural-urban status, and socioeconomic factors; a clinical risk module employing random forest algorithms for traditional risk factors; a mental health module using gradient boosting to capture anxiety-depression patterns; and an outcome prediction module combining all inputs for final risk stratification [18,19].

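### Personal stroke-risk scores are promised from a 1:1 matched case-control sample with no link to population incidence, and the planned calibration checks cannot reveal the resulting overstatement

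*Protocol article*

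**What the plan says.** Materials and methods sets the design: "The FORECAST study is an ongoing ambispective case-control study conducted at the National Institute of Neurosciences and Hospital (NINS&H), Bangladesh". It also fixes the ratio: "The study will enroll 4,000 participants, comprising 2,000 stroke cases and 2,000 matched controls". On the controls it says: "Controls comprise age and sex-matched healthy adults without stroke history, recruited from hospital visitors and community health facilities". Stroke occurrence is the primary outcome.

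Validation is stratified 10-fold cross-validation within this sample, with SMOTE and other resampling against imbalance. Several performance measures are listed, "with target performance exceeding 90% accuracy based on recent advances in stroke prediction modeling". The Statistical analysis part adds conditional logistic regression for the matched data and this: "Model calibration will be assessed using Hosmer-Lemeshow goodness-of-fit tests and calibration plots". No reference population is named for that assessment.

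The Results section then describes the product: "The model will provide personalized risk scores with confidence intervals, enabling clinicians to make evidence-based decisions regarding preventive interventions". It goes on to mention mobile applications for screening in the community, and the Discussion speaks of finding people at high risk before a stroke happens. The limitations in the Discussion cover representativeness, data quality and the lack of external validation. They do not mention that the stroke fraction was fixed by the sampling.

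**The concern.** Sampling on the outcome identifies odds ratios and discrimination. It does not identify absolute risk, which needs an outside incidence over a stated period. The article gives neither, yet offers individual risk scores to guide prevention.

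The planned checks do not close the gap. Stratified folds keep the sampled case mix, and SMOTE moves data towards balance, not towards population incidence. Calibration tests and plots in this sample compare predictions near 50% on average with an observed fraction of 50%. They can pass while the level is wrong for the people who would be screened. The promised confidence intervals would express sampling error around that same wrong level.

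The study's main deliverable is at stake: a model that ranks people correctly could be presented as giving each person's chance of stroke.

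**Working it through.** **Inputs**
- Cases and controls: 2,000 and 2,000 (Materials and methods).
- Sensitivity and specificity: 90% each. This is an assumption, chosen because it corresponds to 90% accuracy, the level of the article's target.
- Population risk π over the horizon of use: not in the article, so assumed from 0.1% to 5%. The 15% and 35% from the sample-size calculation are added because they are the only stroke prevalences stated.

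**Step 1: the sample fraction.** 2,000 / (2,000 + 2,000) = 50%. The arithmetic behind 2,000 has a separate problem: the article's formula gives 69.58, and it then writes 1,740. Only the 1:1 ratio matters here.

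**Step 2: from score to risk.** True odds = score odds × [π/(1−π)] ÷ (cases/controls), and cases/controls = 1. A score of 50% has odds 1, so the true risk is π. A score of 90% has odds 9. At π = 1%, 9 × 0.01/0.99 = 0.0909, and 0.0909/1.0909 = 8.3%. On the logit scale the missing correction, ln[(1−π)/π], is 6.9, 5.3, 4.6 and 2.9 at π = 0.1%, 0.5%, 1% and 5%.

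**Step 3: positive predictive value.** PPV = 0.9π / [0.9π + 0.1(1−π)]. It equals the risk behind a 90% score because 0.9/0.1 is also 9.

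| π | Risk behind a 50% score | Risk behind a 90% score; PPV | False positives per true positive | Accuracy of calling everyone stroke-free |
|---|---|---|---|---|
| 0.1% | 0.1% | 0.9% | 111 | 99.9% |
| 0.5% | 0.5% | 4.3% | 22 | 99.5% |
| 1% | 1% | 8.3% | 11 | 99% |
| 5% | 5% | 32% | 2.1 | 95% |
| 15% | 15% | 61% | 0.6 | 85% |
| 35% | 35% | 83% | 0.2 | 65% |
| 50% (sample) | 50% | 90% | 0.1 | 50% |

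**Step 4: would the planned calibration check notice?** One simulated population with 1% risk and a single predictor was sampled 2,000:2,000 without matching, and a logistic model was fitted. In the sample the mean prediction was 50% and the Hosmer-Lemeshow test did not reject (p = 0.09). In the population the mean prediction was 26.8% against a true 1.0%, about 27-fold too high, and PPV above a cut-off of 0.5 was 4.1%. The fitted slope was 0.99 against a true value of 1, so the ranking was right and only the level was wrong. This is a single run and its p-value is illustrative. The reason is general: both sides of the in-sample comparison carry the same 50% base rate.

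**Step 5: accuracy.** Accuracy = sensitivity × π + specificity × (1−π). At 90%/90% it is 90% for every π. At 95%/87% it is 91% in the 1:1 sample and about 87% at π = 1%. At 87%/95% it is 91% and about 95%. Calling everyone stroke-free scores 1−π, which exceeds 90% whenever π is below 10%.

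**The case against.** The article speaks of risk scores and risk stratification, never of probability or a time horizon, and a relative score can serve stratification. Conditional logistic regression has no intercept and so carries no 50% base rate. A condensed article may leave recalibration to a full plan that is not shown, and the Discussion concedes that the model needs testing elsewhere. AUC, sensitivity, specificity and calibration plots are already planned.

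Part of this stands. It cannot be said that no correction will be made, or that uncorrected clinical use is intended. But Hosmer-Lemeshow tests and calibration plots work on predicted probabilities, so the article does treat the output as one. The point rests on how the stated sampling, calibration method and promised use combine, not on an omitted detail.

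Four stronger readings are not supported:
- A reader might infer that the 50:50 mix inflates accuracy itself. Step 5 shows that accuracy moves only if sensitivity and specificity differ, and then in either direction.
- A reader might infer that the 19 listed variables cap accuracy at about 85%. That figure treats every variable as an independent binary exposure at 35% versus 15%, although the article gives those as stroke prevalences by exposure, for planning. It also counts the matched age and sex and leaves out imaging. Normally distributed predictors with the same split (d = 0.65) give Φ(0.65 × √19 / 2), about 92%.
- A reader might infer that all the study's predictions are affected. The 90-day modified Rankin model uses cases only, so the 1:1 ratio does not distort it.
- A reader might take the smallest predictive values as established. They depend on an assumed risk range; at 15% and 35% the loss is much smaller.

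**Conclusion.** The point holds for the stroke-occurrence model. As described, its scores cannot be read as absolute risks, and the planned calibration cannot show whether they are right for any population. The direction is certain for every population risk below 50%. The size depends on a risk that the article does not state: PPV falls from 90% to between 0.9% and 32% over an assumed 0.1% to 5%, and to 61% or 83% at the article's own planning figures.

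What is overstated is absolute risk, PPV and hence usefulness for screening; discrimination is not. An accuracy target above 90% is not wrong as arithmetic, but it does not demonstrate screening value when π is below 10%. The conclusion assumes that no recalibration is specified elsewhere. If one is, the article's wording should say so.

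**What to change.** - **Results, expected results and clinical impact:** describe the stroke-occurrence output as a relative score unless it is recalibrated to external age- and sex-specific incidence over a stated horizon. Because of the matching, the offset has to be set within age-sex strata: add log[π_s/(1−π_s)] − log(cases_s/controls_s), where π_s is the external risk in stratum s. The ratio must be the one used in training, after any SMOTE; alternatively omit SMOTE for this model. An offset does not repair bias from selecting healthy controls, so calibration in a population cohort remains the real test.
- **Statistical analysis:** label in-sample calibration as sample-based and not as evidence of absolute-risk calibration. Replacing the Hosmer-Lemeshow test is optional, since calibration plots are already planned.
- **Materials and methods:** make AUC with a 95% confidence interval the headline measure in place of the accuracy target, and add PPV and NPV over a range of population risks.

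The cost is revised wording, a short extra analysis and a search for suitable published incidence figures. The headline result will look less favourable. No change to recruitment or data collection is needed.
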